### Endpoints

The primary endpoint will be a composite endpoint of the incidence of EFL after CPB and of PPCs at 5 days after surgery (see Table 2 for complete definition of PPCs). Before/after sternotomy, a PEEP test will provide the best PEEP value, that will be the least value of PEEP for which closing capacity does not exceed the FRC, leading to the avoidance of EFL and atelectasis. In practice, the EFL phenomenon will be assessed at different PEEP levels, until the abrupt decrease in end-expiratory pressure will cause an increment in expiratory flow. At this level the patient will not be flow-limited and this will be considerate his best PEEP for the rest of surgery.

**Table 2 Tab2:** Definition of postoperative pulmonary complications (PPCs), Jammer et al*.* [24]

Complication	Definition
Respiratory infection	Patient has received antibiotics for a suspected respiratory infection and met one or more of the following criteria: new or changed sputum, new or changed lung opacities, fever, white blood cell count > 12 × 10^9^ l^-1^
Respiratory failure	Postoperative PaO_2_ < 8 kPa (60 mmHg) on room air, a PaO_2_:FIO_2_ ratio < 40 kPa (300 mmHg) or arterial oxyhemoglobin saturation measured with pulse oximetry < 90% and requiring oxygen therapy
Pleural effusion	Chest radiograph demonstrating blunting of the costophrenic angle, loss of sharp silhouette of the ipsilateral hemidiaphragm in upright position, evidence of displacement of adjacent anatomical structures or (in supine position) a hazy opacity in one hemithorax with preserved vascular shadows
Atelectasis	Lung opacification with a shift of the mediastinum, hilum, or hemidiaphragm toward the affected area, and compensatory over-inflation in the adjacent non-atelectatic lung
Pneumothorax	Air in the pleural space with no vascular bed surrounding the visceral pleura
Bronchospasm	Newly detected expiratory wheezing treated with bronchodilators
Aspiration pneumonitis	Acute lung injury after the inhalation of regurgitated gastric contents

*PaO*_*2*_ arterial partial oxygen pressure, *FiO*_*2*_ fraction of inspired oxygen

The secondary endpoints will be the evaluation of the following:Readmission to the intensive care unit (ICU)Need for re-intubationNeed for non-invasive ventilationDuration of mechanical ventilationPostoperative infectionsMajor adverse cardiac events (MACE; see Table 3 for complete definition of MACE)Length of the ICU and hospital stay30-day and 1-year mortality

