### Interventions (randomization and treatment protocol)

Once the patient has provided informed consent, the investigator (e.g., the anesthesiologist in the operating theater) logs into a dedicated on-line portal (www.eflvent.it) to obtain the allocation arms. The randomization will be in a 1:1 ratio between the parallel groups, in blocks of 20 patients. From that moment, the online data will be anonymous and, in any event, the patient will be analyzed according to the “intention-to-treat” principle.

To reduce the bias, data will be collected by trained observers, trained accordingly to Good Clinical Practice (GCP) guidelines [16, 17], who will not participate to patient care. Furthermore, we decided to focus on clinically relevant data that cannot be influenced by physician management. Caregivers will be interviewed daily about the occurrence of postoperative adverse events. The patients will be blinded to the allocation arm.

All patients will receive lung protective ventilation, with a tidal volume of 7 ml/Kg of ideal body weight (IBW), a respiratory frequency titrated to maintain normocapnia, assessed by seriated blood-gas analyses. FiO_2_ will never be higher than 80%, except for the blood samples obtained for shunt fraction calculation.

Patients will be randomized, immediately before surgery, to receive either a PEEP equal to the best PEEP, assessed with a PEEP test, immediately after the induction of anesthesia or to zero. All patient will be furthermore randomized to receive either a CPAP equal to the best PEEP or a zero PEEP strategy (with disconnection from anesthesia circuit) during CPB. The two randomizations will be independent each from other.

During CPB our goal will be to maintain PaO_2_ between 200 and 250 mmHg in order to avoid hyperoxia-induced lung injury; moreover, the hematocrit will be maintained above 24% [18].

During weaning from CPB we will perform a single alveolar recruitment maneuver (RM). This RM will be performed manually by the anesthesiologist with a gas mixture of oxygen and air (with an inspired oxygen fraction lower than 80%) at the end of procedure. After CPB, this RM will be performed manually, in correspondence to the surgical de-airing procedure. Airway pressure will be kept at 40 cmH_2_O for at least 10 s. The flowchart in figure 2 (Fig. 2) resume the enrollment and allocation process.

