### EFL determination

The determination of EFL during general anesthesia and neuromuscular blockade will be performed using the PEEP test. This test is based on a sudden decrease of expiratory resistance obtained by a subtraction of 3 cmH_2_O of PEEP during expiration (Fig. 3). A patient will be considered to have EFL if reducing PEEP by 3 cmH_2_O will not increase expiratory flow when compared with the previous breath (panel B). If expiratory flow will increase with PEEP reduction, the patient will be considered not flow limited (panel A). All loops will be saved in electronic format for further analysis.

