### Postoperative ventilation

Mechanical ventilation setting used during patient transfer from the operating theater to the ICU will be reported in appropriate case report form (CRF). In the ICU it will be applied a volume-controlled continuous mandatory ventilation (VC-CMV) with the same parameters used in the operating room. Blood oxygen saturation will be constantly monitored with a pulse oximeter; blood-gas analyses will be performed according to clinical needs.

Following data will be collected: extubation time, duration of mechanical ventilation and need for re-intubation.

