### Statistical considerations

#### Sample size

Sample size calculation was based on a two-sided α error of 0.05 and a 80% power (β). On the basis of our experience, we anticipate that the 50% of patients with ventilation cessation during CPB and no PEEP before and after CPB will reach the composite endpoint of EFL after CPB and respiratory complications at 5 days, while only the 30% of the patients treated with an optimal ventilatory strategy will develop this composite endpoint. Including a drop-out fraction of 10%, we will enroll 51 patients per group, 204 in total.

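### The stated bias safeguard, that the trial's data lie beyond physicians' influence, does not fit a primary endpoint that depends in part on treatment decisions, discretionary blood gases and judgement in reading loops

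*Protocol article*

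**What the plan says.** The Trial design section calls the trial single-blind, and the Interventions section names only the patients as blinded. The investigator who obtains the allocation from the portal is, for example, the theatre anesthesiologist. Two measures against bias are then given. First, data are collected by trained observers who take no part in care. Second, "we decided to focus on clinically relevant data that cannot be influenced by physician management". Caregivers are also interviewed each day about adverse events.

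The Endpoints section makes the primary endpoint a composite of EFL after CPB and postoperative pulmonary complications (PPCs) at 5 days. Table 2 defines seven PPCs. Respiratory infection begins with "Patient has received antibiotics for a suspected respiratory infection". Bronchospasm is "Newly detected expiratory wheezing treated with bronchodilators". Respiratory failure can be met on PaO2, on the PaO2:FiO2 ratio, or on low saturation with a need for oxygen therapy. In the Postoperative ventilation section, "blood-gas analyses will be performed according to clinical needs".

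Under EFL determination, a patient is flow limited if taking away 3 cmH2O of PEEP does not raise expiratory flow relative to the preceding breath. The legend of Fig. 3 adds that a short early rise in flow is to be disregarded. The same section states that "All loops will be saved in electronic format for further analysis".

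**The concern.** The sentence in the Interventions section tells the reader that the outcome data are protected from the behaviour of clinicians who know the arm. If that were true, masking of outcome assessment would matter little. If it is not true for the primary endpoint, one of the few safeguards stated in the article is empty.

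Differential detection or classification is then possible in both halves of the composite. A clinician who knows that a patient had zero PEEP may take more gases, start treatment sooner, or read an ambiguous loop as flow limited. More gases give more chances of crossing a PaO2:FiO2 limit. The main hypothesis under Objectives favours best PEEP and CPAP, so any such difference would tend to run in the expected direction.

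**Working it through.** **1. Set the safeguard beside the endpoint.**

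| Component of the primary endpoint | Does it depend on management or judgement? |
|---|---|
| Respiratory infection | Yes: antibiotics must have been given, together with at least one clinical, imaging or laboratory sign |
| Bronchospasm | Yes: bronchodilators must have been given |
| Respiratory failure | In part: the saturation route requires oxygen therapy, and the PaO2 routes require a gas, taken by clinical need after surgery |
| Pleural effusion, atelectasis, pneumothorax, aspiration pneumonitis | The definitions name no treatment decision |
| EFL after CPB | Judgement: loops are compared between breaths, with no numeric threshold and an early transient to be discounted |

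Two of seven PPC definitions strictly require a treatment, a third does so by one route, and four do not. The safeguard is therefore untrue for part of the PPC half. The EFL half involves a judgement, whoever makes it. Several secondary endpoints (re-intubation, non-invasive ventilation, duration of ventilation, ICU and hospital stay) also reflect management.

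**2. Reproduce the planned size, to get the number per margin.** Inputs from the Sample size section: rates of 50% and 30%, two-sided 5% level, 80% power, 10% drop-out. With unpooled variance:

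n = (1.960 + 0.842)² × (0.50 × 0.50 + 0.30 × 0.70) / 0.20² = 90.3, so 91 per margin.

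91 / 0.9 = 101.1, so 102 per margin, 204 in total and 51 per cell. This matches the article. The point made here does not change that figure. After drop-out, 102 × 0.9 = 91.8, about 92 evaluable patients per margin.

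**3. Illustrate what one-sided flagging could do.** Assume no true effect and the same true rate p in both levels of a factor. Assume also that a fraction b of true non-events is called as events in the control level only. Then:

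- observed control rate: p_c = p + b(1 − p)
- d = p_c − p, and p̄ is the mean of the two rates
- se0 = √[2 p̄(1 − p̄)/92]
- se1 = √{[p_c(1 − p_c) + p(1 − p)]/92}
- rejection rate = Φ[(d − 1.96 se0)/se1] + Φ[(−d − 1.96 se0)/se1]

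For p = 0.40 and b = 0.10: p_c = 0.40 + 0.60 × 0.10 = 0.46, d = 0.06, se0 = √(2 × 0.43 × 0.57/92) = 0.073 and se1 = 0.073. The rejection rate is about 0.13.

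| True rate p | b = 5% | b = 10% | b = 15% |
|---|---|---|---|
| 50% | 52.5% vs 50%: 6% | 55% vs 50%: 10% | 57.5% vs 50%: 17% |
| 40% | 43% vs 40%: 7% | 46% vs 40%: 13% | 49% vs 40%: 23% |
| 30% | 33.5% vs 30%: 8% | 37% vs 30%: 17% | 40.5% vs 30%: 32% |

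Each cell gives the observed rates and then the two-sided rejection rate at a nominal 5%. The true rates span the article's planning values. The values of b, and the assumption that flagging occurs in one arm only, come from no document. Yates' correction, which Data analysis allows where appropriate, is not applied here.

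**The case against.** A reader might infer that the protocol admits to unmasked outcome collection and uses this sentence to justify it. It does neither. The sentence is added to another safeguard, the observers outside patient care, and the masking of those observers is simply not stated. The article condenses a full protocol, which may cover masking or adjudication, so silence on it is not itself a fault.

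A reader might also infer that the whole PPC endpoint consists of physicians' decisions. Four of the seven definitions name none. Infection also needs a sign, respiratory failure can be met on measured values, and saturation is monitored continuously. The definitions follow a stated European standard (Trial organization).

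A third tempting inference is that the operator reads EFL in theatre with knowledge of the arm. The article names no reader, and saving the loops leaves later reading open.

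These objections limit the point but do not remove it. Separation from care is not the same as masking, and a standard definition can still depend on a treatment decision. Whatever the full protocol provides, the sentence remains untrue of the endpoint defined in the same article. Ventilation cannot be masked from the theatre team, but the reading of saved loops can be masked.

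**Conclusion.** The point holds in a limited form: a stated safeguard is contradicted by the article's own endpoint definitions. The primary endpoint depends in part on management and, for EFL, on judgement, while only patients are named as blinded. The contradiction rests on the text alone and needs no assumption.

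The possible size of the bias does rest on assumptions. The range of about 6% to 32% shows what 5–15% one-sided extra flagging would do at true rates of 30–50% with 92 patients per margin. It is not an estimate for this trial, and no single value in it should be quoted as the trial's error rate. The planned 204 patients are unaffected. The change is worth making because it is cheap, and the Current trial status section places the start of recruitment in the future.

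**What to change.** 1. **Withdraw or reword the sentence in the Interventions section.** Say instead that some components depend on treatment decisions or on reading of loops, and state how assessment is protected.
2. **Define endpoint EFL by a masked reading.** File the saved loops under study code with arm and PEEP setting hidden. Have them classified by an existing trained observer who was not in theatre. Keep the live reading for care only, since PEEP in the ICU depends on EFL status at arrival, and state that the masked reading defines the endpoint. Report how often the two disagree.
3. **Where feasible, restrict the online CRF.** Hide the allocation field and the intraoperative ventilation fields from the observer who records PPCs; hiding allocation alone would leave PEEP visible. Leave the clinical handover unchanged.
4. **Consider a sensitivity analysis.** Omit PPCs that rest only on discretionary gases or on treatment decisions. Limiting the oxygenation criterion to scheduled gases would not work: those listed under Shunt fraction calculation end before the patient leaves the operating room, and none is scheduled afterwards.

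The cost is some reading after surgery, a filing rule for the loops and a change to portal permissions. Observers may need instruction in classifying loops, because the article mentions only their GCP training. Some masked readings may disagree with the live ones. The CRF restriction will not mask fully, because an observer may still learn the arm from caregivers.

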**Fig. 2 Fig2:**
[figure not shown]
The trial flowchart. Description of the ventilatory strategies and allocation of patients before, during, and after cardiopulmonary bypass

### EFL determination

The determination of EFL during general anesthesia and neuromuscular blockade will be performed using the PEEP test. This test is based on a sudden decrease of expiratory resistance obtained by a subtraction of 3 cmH_2_O of PEEP during expiration (Fig. 3). A patient will be considered to have EFL if reducing PEEP by 3 cmH_2_O will not increase expiratory flow when compared with the previous breath (panel B). If expiratory flow will increase with PEEP reduction, the patient will be considered not flow limited (panel A). All loops will be saved in electronic format for further analysis.

**Fig. 3 Fig3:**
[figure not shown]
The PEEP test. Flow-volume loops of patients undergoing positive end-expiratory pressure (PEEP) test. **a** Subtraction of 3 cmH_2_O of PEEP in this cohort of patients leads to an increase of expiratory flow: these patients are classified as not flow-limited. **b** Subtraction of 3 cmH_2_O of PEEP does not increase expiratory flow, except for a brief, initial, transient increase, which is mainly the result of a sudden reduction of volume of the upper airways and denotes flow limitation. See text for further explanations

EFL will be determined at the following time-points:After anesthesia inductionAfter sternotomyDuring CPB, immediately before the RMAfter the RMBefore sternosynthesisBefore discharge from operating room

After ICU arrival, a best PEEP will be determined in patients having EFL and set for all the postoperative ICU stay. The best PEEP will be defined as the PEEP value able to eliminate EFL, assessed with the same method of the PEEP test. Patients without EFL at arrival in ICU will be ventilated with a PEEP of 5 cmH_2_O. An overview of measurements is provided in Table 4.

**Table 4 Tab4:** Synopsis of measurements

	Presence of EFL	Lung compliance	Airway resistance	BGA	Shunt percentage
Before sternotomy	X	X	X	X	X
After sternotomy	X	X	X	X	
Before recruitment maneuver	X	X	X		
After recruitment maneuver	X				
Before sternosynthesis	X	X	X	X	
After sternosynthesis	X	X	X	X	X

*BGA* blood-gas analysis, *EFL* expiratory flow limitation

#### Lung mechanics determination [19]

Quasi-static compliance of the respiratory system (Cqst,rs) will be calculated as:$$ \mathrm{Tidal}\ \mathrm{volume}/\left(\mathrm{End}\ \mathrm{inspiratory}\ \mathrm{plateau}\ \mathrm{pressure}- PEEPtot\ \left(\mathrm{ml}/{\mathrm{cmH}}_2\mathrm{O}\right)\right), $$

where *PEEPtot* is the end-expiratory pressure at period of no flow. Measurement will be performed with an inspiratory pause of 60%.

Dynamic compliance of respiratory system (Cqdyn,rs), induced by thorax opening, will be calculated as:

$$ \mathrm{Tidal}\ \mathrm{volume}/\left(\mathrm{End}\ \mathrm{inspiratory}\ \mathrm{peak}\ \mathrm{pressure}- PEEPtot\ \left(\mathrm{ml}/{\mathrm{cmH}}_2\mathrm{O}\right)\right) $$

Measurement will be performed with an inspiratory pause of 10%.

Airway resistance (Rmin,rs) will be calculated as:$$ \left( Ppeak-{P}_1\right)/{V}^{'}, $$

where *Ppeak* is the peak inspiratory pressure, *P*_1_ is the airways’ pressure at the point of zero flow and *V*′ is the inspiratory flow. Measurement will be performed with an inspiratory pause of 60%. Lung mechanics will be determinate immediately after every PEEP test execution.

#### Dead space calculation

Dead space fraction calculation will be performed with the Enghoff modification of the Bohr equation:$$ Vd/ Vt=\left({PaCO}_{2-}\ {PECO}_2\right)/{PaCO}_2, $$

where:*Vd* is the dead space*Vt* tidal volume*PECO*_*2*_ is pressure of mean expired CO_2_

#### Shunt fraction calculation

Shunt fraction will be determined before surgery and after surgery in the operating room during general anesthesia, before patient discharge from operating room. Shunt fraction will be assessed as follows in all patients:$$ Qs/ Qt=\left({PAO}_2-{PaO}_2\right)\times 0.0031/C\left(a- vmixed\right){O}_2+\left[\left({PAO}_2-{PaO}_2\right)\times 0.0031\right], $$

where:*PAO*_*2*_ is oxygen alveolar concentration*PaO*_*2*_ is oxygen arterial concentration*C(a-vmixed)O*_*2*_ is arteriovenous difference in oxygen concentration0.0031 is a conversion factor to volume percent for O_2_

Measure will be performed while breathing 100% oxygen for 20 min, to achieve a complete hemoglobin saturation.

If a PAC is placed, according to clinical indications, the shunt fraction will be calculated from the following formula:$$ Qs/ Qt={ CcO 2}_{-}\ {CaO}_2/{CcO}_2- Cv(mixed){O}_2\times 100, $$

where:*CcO*_*2*_ is pulmonary capillary blood O_2_ content, estimated with the following equation:

$$ {CcO}_2=\left(\mathrm{Hb}\times 1.34\right)+\left(0.0031\times {PAO}_2\right), $$
*CaO*_*2*_ is arterial oxygen content*Cv(mixed)O*_*2*_ is oxygen content in blood samples obtained from the pulmonary artery*PAO*_*2*_ is alveolar oxygen partial pressure

Blood samples will be collected from the arterial catheter and the pulmonary artery catheter, under a FiO_2_ of 100% in the same moment.

Furthermore, blood-gas analyses (BGA) will be performed on arterial blood:After anesthesia inductionAfter sternotomy, together with heparinizationBefore sternosynthesis, together with protamine administrationBefore discharge from the operating room

### Postoperative ventilation

Mechanical ventilation setting used during patient transfer from the operating theater to the ICU will be reported in appropriate case report form (CRF). In the ICU it will be applied a volume-controlled continuous mandatory ventilation (VC-CMV) with the same parameters used in the operating room. Blood oxygen saturation will be constantly monitored with a pulse oximeter; blood-gas analyses will be performed according to clinical needs.

Following data will be collected: extubation time, duration of mechanical ventilation and need for re-intubation.

### Intraoperative monitoring

Intraoperative monitoring will include: electrocardiogram (ECG), pulse oximeter, capnography, urine output, invasive blood pressure measurements, advanced hemodynamic monitoring (pulmonary artery catheter (PAC)/transesophageal echocardiogram (TEE)), bladder or esophageal temperature, and activated clotting time (ACT).

The anticoagulant protocol in our center is as follows: heparin (3 mg/Kg) to achieve an ACT of 200 s for cannulation and 480 s to proceed with the CPB. At the end of the CPB, protamine (3 mg/Kg) is used (ACT target < 150). In case of allergy to heparin, we will administer bivalirudin.

During CPB, pump flow of 2.5 L/min/m^2^ and mild hypothermia (31–33 °C) will be applied.

The following ventilatory parameters will be monitored: TV, PEEP, FiO_2_, peak airway pressure (Paw), and plateau pressure (Pplat).

### Data collection

All the data will be collected on the dedicated CRF. No personal information of the patients will be included in the database. All patients will receive a code at the moment of randomization and it will be used for the storage in the online database. Data will be stored pseudo-anonymously and only the investigators will be able to match patients’ names and the codes.

Data collection will include:Preoperative information: anamnesis, physical examination, cardiac and pulmonary function, laboratory analysisIntraoperative data: ventilatory parameters, type of anesthesia, type of cardioplegia, type of CPB circuit, temperature during CPB, use of volatile anesthetics in CPB, volume and type of fluids administered, transfusion requirements, use of vasoactive drugs, duration of intervention, ventilation mode used during transport to the ICUPostoperative data: use of inotropic or vasoactive drugs, mechanical devices, time to extubation, need for respiratory support or re-intubation, and hospital stay

In addition, the standard cardiac surgery risk scores, Euroscore I–II [20, 21], the ACEF score [22] and the ARISCAT score [23], will be calculated.

Regular backups will be also done in order to minimize the risk of data corruption.

### Follow-up variables

Follow-up will be performed at 30 days and at 1 year. After discharge from the hospital, patients will be phoned for the follow-up. Any readmission to hospital or Exitus will be recorded as well as information related to major pulmonary complications.

